# Study Outcome Measures (Endpoints)

## 3.1 Safety Endpoints

**Primary Endpoints:** The vaccine safety profiles will be assessed according to:

- Number, severity and percentage of participants with solicited and/or unsolicited local and/or systemic adverse reactions during a 7-day period post each vaccination.

**Secondary Endpoints:** The following safety parameters will be followed:

- Number and percentage of participants with unsolicited adverse reactions for 28 days post each vaccination.
- All serious adverse events (SAEs) occurring over the study period.

**Exploratory Endpoints:** The following safety parameters will be followed:

- All adverse events of special interest (AESIs) as listed in Annex A occurring over the study period.

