Participants will be contacted by phone (contact C3) on 194 (+7) daysafter administration of second dose of study product for the closure of any ongoing AEs and concomitant medications; and (b) collection of any SAEs or AESIs and new concomitant medications, if associated with the SAE/ AESI reported. This will complete participant participation in the study, however, if the participant reports any health problems, the PI may use his or her medical judgment and ask the participant to come to the clinic for an examination or any necessary testing.

Safety data review in this study is performed by a DSMB. Safety oversight is described in more detail in section 9.7.

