## 7.3 Final Study Call (contact C3)

## The contact C3 is schedule for day V2+194 and it is the last contact with the participant.

1. The participant will be contacted via telephone and identity confirmed.
2. Study staff will review interim medical histories and concomitant medications with the participant since these were last updated. No new concomitant medication will be recorded unless it relates to a newly identified SAE/AESI.
3. Study staff will ask about any medical event that would constitute an SAE since the last visit.
4. Study staff will ask if the participant has been hospitalized or had any new medically confirmed disease(s) since the last visit. Study staff will review any AESIs and report accordingly. If deemed clinically necessary, a visit to the study site will be scheduled.
5. No new AE information will be recorded unless it qualifies as an SAE or an AESI.
6. If an SAE/AESI is reported, the clinician should record the event on the appropriate form, notify the entities who require notification, and refer the participant for treatment of the SAE/AESI, if warranted. Study staff may request to review any document related to participant´s visits or hospitalizations handed to study staff by participants (e.g.: hospital discharge summaries, etc), and considered relevant to the assessment of the SAE and if permitted by the participant, extra information may be requested by study staff to other health care services/providers.
7. After recording the information, the participant will be discharged from the study.

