## 9.3 Methods and Timing for Assessing and Recording Safety Parameters

### 9.3.1 Adverse Events

The occurrence of an AE might come to the attention of study personnel during study visits and interviews of a study participant presenting for medical care. Information to be collected on AEs includes event description, time of onset, clinician’s assessment of severity, relationship to study product, and time of resolution/stabilization of the event. AE assessment should be made only by those with the training and authority to make a diagnosis.

Any medical condition that was present at the time that the participant was enrolled should not be reported as an AE, but should be reported as a pre-existing condition on the Medical History Form. However, if this condition occurs with greater frequency or severity during the study, it should be recorded as an AE.

AEs, including laboratory abnormalities that are Grade 2 and above, should always be assessed for severity and relationship to study products.

This study will collect and record solicited and unsolicited local and systemic AEs (described in further detail in section below). For clarity, solicited AEs refer specifically to those asked about during the 7-day post study injection period. Unsolicited events are those not specifically solicited, but may be reported by the participant at any time or observed by study staff while the participant is at a clinic for a study visit. Unsolicited events are recorded up through 28 + 7 days post each study injection, except for SAEs, which are recorded throughout the entire study period as required (V2+194 days). If a new solicited event is reported by the participant outside of the 7-day post-vaccination window, this event will be recorded as an “unsolicited AE” because it will be outside of the 7-day window for collection of solicited reactogenicity.

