### 9.3.8 Procedures for Out-of-range Laboratory Test Values

Out-of-range laboratory values and AEs. To the extent possible, all reference ranges for clinical laboratory test results will be pre-specified. The site staff will follow the Toxicity Table (Table 5). Laboratory values that are out-of-range will not be considered an AE unless they qualify as a Grade 2 or above on the Toxicity Table. The reference ranges for the laboratory will be taken in to consideration when determining out of range results.

Out-of-range test values may be considered an SAE if two circumstances are met:

1. the value rises to the level of Potentially Life-threatening (Grade 4), and
2. the event is determined by the Principal Investigator to pose an immediate risk of death.

A Grade 4 laboratory result does not, in and of itself, constitute an SAE. Grade 4 places a laboratory value as a potentially life-threatening event, but a Grade 4 laboratory result should not be reported as an SAE unless the PI has determined that it does, in fact, pose an immediate risk of death.

Assessing relatedness and clinical significance of out-of-range laboratory values: All laboratory results should be reviewedAny laboratory finding Grade 2 and above is regarded as an AE. The investigator will assess relatedness and clinical significance for these findings.

Clinical judgment always should be used to determine whether a laboratory result requires additional follow up. However, the investigator should redraw any Grade 2 or above laboratory result that is deemed clinically significant at an unscheduled visit to check if the result has normalized.

Any Grade 2 or above laboratory value that is clinically significant and has not returned to normal or stabilized by day V2+194 should be marked by the investigators as “continuing” or “unresolved.” The investigator should assure that the participant is referred for appropriate medical follow-up, if indicated.

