## 11.5 Analysis of Safety Endpoints:

The safety profiles will be evaluated by the proportion of subjects experiencing AEs, related or not related, of the following four categories:

- Immediate reactions occurring within 30 minutes of administration of any dose, measured as observed by study staff or reported by the subject to study staff.
- Adverse events (reactogenicity) commonly associated with intramuscular vaccination (solicited local and systemic reactions) occurring through 7 days following any dose, measured as observed by study staff or reported by the subject to study staff.
- All other adverse events (including unsolicited events) following any dose, measured as observed by study staff or reported by the subject to study staff over the entire study period. This includes clinical findings and abnormal laboratory findings from blood specimens collected on Days 7 and 35.
- All serious adverse events (SAEs) occurring throughout the study period, as observed by study staff, reported by the subject to study staff, or noted by the subject diary card. This includes clinical findings and Grade 4 abnormal laboratory findings from blood specimens collected on Days 7 and 35 considered as life threatening.
- All adverse events of special interest (AESIs) occurring throughout the study period, as observed by study staff, reported by the subject to study staff, or noted by the subject diary card. This includes clinical findings and Grade 4 abnormal laboratory findings from blood specimens collected on Days 7 and 35 considered as life threatening.

Counts of all events will be reported and summarized according to event severity, as “any local AE”, or “any systemic AE”, and by relationship to administration of study product, as deemed by a blinded study clinician. Percentages of subjects experiencing each reaction or event, or at least one reaction or event will be calculated along with two-sided exact 95%CIs.

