# Annex A: List of Adverse Events of Special Interest

Gastrointestinal disorders

- Celiac disease
- Crohn’s disease
- Ulcerative colitis
- Ulcerative proctitis

Liver disorders

- Autoimmune cholangitis
- Autoimmune hepatitis
- Primary biliary cirrhosis
- Primary sclerosing cholangitis

Metabolic disease

- Addison’s disease
- Autoimmune thyroiditis (including Hashimoto thyroiditis)
- Diabetes mellitus type I
- Grave’s or Basedow’s disease

Musculoskeletal disorders

- Antisynthetase syndrome
- Dermatomyositis
- Juvenile chronic arthritis (including Still’s disease)
- Mixed connective tissue disorder
- Polymyalgia rheumatic
- Polymyositis
- Psoriatic arthropathy
- Relapsing polychondritis
- Rheumatoid arthritis
- Scleroderma, including diffuse systemic form and CREST syndrome
- Spondyloarthritis, including ankylosing spondylitis, reactive arthritis (Reiter’s Syndrome) and undifferentiated spondyloarthritis
- Systemic lupus erythematosus
- Systemic sclerosis

Neuroinflammatory disorders

- Acute disseminated encephalomyelitis, including site specific variants (e.g. non-infectious encephalitis, encephalomyelitis, myelitis, myeloradiculomyelitis)
- Cranial nerve disorders, including paralyses/paresis (e.g.Bell’s palsy)
- Guillain-Barré syndrome, including Miller Fisher syndrome and other variants
- Immune-mediated peripheral neuropathies and plexopathies, including chronic inflammatory demyelinating polyneuropathy, multifocal motor neuropathy and polyneuropathies associated with monoclonal gammopathy
- Multiple sclerosis
- Narcolepsy
- Optic neuritis
- Transverse Myelitis

Skin disorders

- Alopecia areata
- Autoimmune bullous skin diseases, including pemphigus, pemphigoid and dermatitis herpetiformis
- Cutaneous lupus erythematosus
- Erythema nodosum
- Morphoea
- Lichen planus
- Psoriasis
- Sweet’s syndrome
- Vitiligo

Vasculitides

- Large vessels vasculitis including: giant cell arteritis such as Takayasu’s arteritis and temporal arteritis.
- Medium sized and/or small vessels vasculitis including: polyarteritis nodosa, Kawasaki’s disease, microscopic polyangiitis, Wegener’s granulomatosis, Churg-Strauss syndrome (allergic granulomatous angiitis), Buerger’s disease thromboangiitis obliterans, necrotizing vasculitis and anti-neurophil cytoplasmic antibody (ANCA) positive vasculitis (type unspecified), Henoch–Schönlein purpura, Behçet's syndrome, leukocytoclastic vasculitis.

Others

- Antiphospholipid syndrome
- Autoimmune hemolytic anemia

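### Section 11.5 counts Grade 4 life-threatening laboratory findings as AESIs although 3.1 limits AESIs to Annex A, and the recording exception in 9.3.1 omits AESIs, contrary to sections 4 and 7.3

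*Protocol*

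**What the plan says.** **What counts as an AESI.** Section 3.1 gives the exploratory safety endpoint as "All adverse events of special interest (AESIs) as listed in Annex A occurring over the study period". Annex A lists named conditions by organ system (for example Guillain-Barré syndrome, uveitis, autoimmune hepatitis). It contains no laboratory parameter and no toxicity grade.

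**What is analysed.** Section 11.5 counts "All adverse events of special interest (AESIs) occurring throughout the study period, as observed by study staff" or reported by the subject. It then adds: "This includes clinical findings and Grade 4 abnormal laboratory findings from blood specimens collected on Days 7 and 35 considered as life threatening". The same sentence closes the SAE bullet immediately above.

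**Where Grade 4 laboratory results are handled.** Section 9.3.8 says "A Grade 4 laboratory result does not, in and of itself, constitute an SAE". Such a result may be an SAE only if it reaches Grade 4 and the principal investigator also judges that it poses an immediate risk of death. AESIs are not mentioned there.

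**How long events are recorded.** Section 9.3.1: "Unsolicited events are recorded up through 28 + 7 days post each study injection, except for SAEs". The list in section 9.2 makes the same split between unsolicited events and SAEs and leaves AESIs out. For the last contact (C3, V2+194), section 4 provides for "collection of any SAEs or AESIs and new concomitant medications, if associated with the SAE/ AESI reported", and section 7.3 says "No new AE information will be recorded unless it qualifies as an SAE or an AESI". Section 9.4.2 requires a dedicated form for every AESI, related or not, with no time limit.

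**The concern.** Section 11.5 fixes the content of an analysis category, and that content does not match the endpoint it is meant to summarise. A Grade 4 creatinine judged life threatening, with no listed condition behind it, lies outside the endpoint in 3.1 but inside the AESI category of 11.5. Two analysts working from the two sections could report different AESI percentages from the same data.

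AESIs are the protocol's specific look at immune-mediated harm. The antigen has not been given to humans with either adjuvant before (section 1.6.1), and IB160 has not been in a clinical trial (section 1.1). In arms of 54, one event that does not belong is visible in the table. Both laboratory draws, Days 7 and 35, fall before visit I, so a misplaced event could also appear in the safety data for the second DSMB review in section 11.6, which supports the choice of candidate for Phase II.

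The recording rule is a second, separate mismatch. AESIs are not among the solicited reactions, so under section 9.3.6 they are unsolicited events. Section 9.3.1 taken by itself would then apply the 28 + 7 day limit to any AESI that is not serious.

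**Working it through.** **Figures in the plan.** The protocol states no expected rate of AESIs or of Grade 4 laboratory findings, so there is no AESI figure to reproduce. Its only safety calculation is Table 8, the probability of seeing at least one event, 1 − (1 − p)^N. It reproduces: N = 54, p = 5% gives 93.7% (stated 94%); N = 162, p = 1% gives 80.4% (stated 80%). Nothing in it is disputed.

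**Part 1: the AESI definition**

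| Source | Content of the AESI category |
| --- | --- |
| 3.1 | Events on the Annex A list, over the study period |
| Annex A | Diagnoses only |
| 11.5, AESI bullet | AESIs, said to include Grade 4 life-threatening laboratory findings |
| 11.5, SAE bullet | Ends with the identical laboratory sentence |
| 9.3.8 | Grade 4 plus immediate risk of death may be an SAE; AESIs not mentioned |

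The laboratory sentence fits 9.3.8 in the SAE bullet. In the AESI bullet it has no support in 3.1, Annex A or 9.3.8. It was probably carried over from the bullet above; that is an inference, and the mismatch does not depend on it.

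Size of one misplaced event, with planned numbers from Table 3 and the exact 95% intervals named in 11.5:
- One arm, N = 54: 0/54 (upper limit 6.6%) becomes 1/54 = 1.9% (0.05% to 9.9%).
- Three doses of one adjuvant pooled, N = 3 × 54 = 162: 1/162 = 0.6%.

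**Part 2: the recording window**

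Nominal days from V1 (Table 1): V2 = 28; visit I = 28 + 28 = 56; C3 = 28 + 194 = 222.

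- If 9.3.1 were the only rule, recording of non-serious AESIs would end at V2+35. That leaves 194 − 35 = 159 days, and 159/222 = 72% of nominal follow-up. Without the +7 it would be 194 − 28 = 166 days, or 75%.
- It is not the only rule. Section 4 collects AESIs at C3. Section 7.3 has staff review AESIs at C3 and record new ones, with no seriousness condition. Section 9.4.2 requires a form for all of them. Under these procedures the gap is 0 days.

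What remains is a conflict of wording: 9.3.1 and 9.2 omit AESIs, while 3.1, 4, 7.3 and 11.5 collect or count them to the end of the study.

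**The case against.** On the definition, the subject of the 11.5 bullet is AESIs, which 3.1 has already defined. The added sentence could be read as describing the kinds of finding that may occur within that set. Several Annex A conditions can also show up in the trial's own laboratory panel: autoimmune thrombocytopenia, autoimmune hemolytic anemia, autoimmune hepatitis and autoimmune glomerulonephritis. A Grade 4 creatinine could reflect the last of these. This stands as a reason not to insist on outright deletion. It does not remove the contradiction, because the sentence has no such limit and the listed event is the diagnosis, not the grade.

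A reader might also infer that counting one event as both SAE and AESI is the error. It is not: section 9.4.2 foresees an AESI that is also an SAE, and the categories in 11.5 are not stated to be exclusive. The error is only that an event outside Annex A is admitted.

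On importance, the objection largely stands. The endpoint is exploratory, the analysis is descriptive, no halting rule in 9.6 names AESIs, and the laboratory event would already be reported as an SAE. The trigger is narrow: two draws, in adults excluded at screening for Grade 2 or worse values. AESIs have their own form and events are tabulated by MedDRA term, so a stray laboratory event would be recognisable.

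On recording, a reader might infer from 9.3.1 that non-serious AESIs are lost for 72% of follow-up. The documents do not support that. Sections 4, 7.3 and 9.4.2 keep collection open to V2+194, so a non-serious AESI arising late is asked about and recorded at C3.

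**Conclusion.** Section 11.5 is wrong as written: it brings Grade 4 life-threatening laboratory findings into a category that 3.1 confines to Annex A. Each misplaced event adds 1.9 percentage points to an arm of 54, or 0.6 to a pooled adjuvant group. How often this would happen cannot be judged from the protocol; that it is rare in screened healthy adults is an assumption.

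The exception in 9.3.1 contradicts sections 3.1, 4, 7.3 and 11.5, but no loss of data is demonstrated and the AESI count cannot be called truncated. The residual risk is that a site applying 9.3.1 leaves a non-serious AESI unrecorded until C3, since no contact is scheduled between visit I and C3.

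Overall importance is low to moderate. Neither part affects a primary or secondary endpoint.

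**What to change.** 1. In section 11.5, define the AESI count as events meeting Annex A over the study period, as in 3.1. Delete the laboratory sentence from that bullet, or limit it to laboratory findings that support an Annex A diagnosis. Leave it in the SAE bullet, where it agrees with 9.3.8.
2. Reconcile the recording exception in 9.3.1, and the list in 9.2, with sections 4 and 7.3, so that sites have a single recording rule for AESIs.

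The cost is a few wording changes. No added visit, sample or form is needed, because 7.3 and 9.4.2 already provide for collecting the data.

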## 11.6 Interim analysis

The DSMB will conduct a formal review (first interim analysis) of the safety data of the first 100 participants (visit S1, safety data). They will either recommend continued enrollment of the remaining participants, modification, or discontinuation of enrollment. Enrollment may continue while this review is being conducted, if no halting rules have been met. The review is not required to be completed prior to receipt of the second study injection unless one of the halting rules has been met.

The DSMB will conduct a formal review (second interim analysis) of the safety data of all participants of the study after safety visit I. This analysis will also include preliminary immunogenicity data to support the decision of the Sponsor for the vaccine candidate in each adjuvant group that will move forward to a future Phase II.

# Data Handling and Record Keeping

## 12.1 Data Capture Methods

This study uses an electronic data capture system - OpenClinica® Enterprise version 3.1 or later

*eCRF*

Electronic CRFs will be developed and data will be managed to the extent possible in accordance with internationally agreed-upon standards, such as the Clinical Data Acquisition Standards Harmonization, which defines basic standards for the collection of clinical trial data, and/or The Society for Clinical Data Management’s Good Clinical Data Management Guidelines.

All the information required by the study protocol will be recorded in eCRF. All data must be derived from source documents. investigator site staff will enter and edit the data via a secure network, with secure access features (username, password and secure identification or username and password – an electronic password system). A complete electronic audit trail will be maintained. The investigator will approve the data using an *electronic signature* (Ref: 21 TheCFR Part 11), and this approval is used to confirm the accuracy of the data recorded. In case electronic CRFs (eCRFs) will be used, the investigator’s data will be accessible from the investigator’s site throughout the trial.

The electronic CRFs must be kept current to reflect patient status at each phase during the course of the trial. The patients must not be identified on the electronic CRF by name. Appropriate coded identification (i.e. Participant Number) must be used. The investigator must make a separate confidential record of these details (participant identification code list) to permit identification of all patients enrolled in a clinical trial in case follow-up is required.

All changes will be requested from the investigator through the EDC system. The investigator’s signature is requested to show he/she agrees with the change that was made. The investigator will be responsible for retaining all records pertaining to the trial as specified in the appropriate contract.

Clinical safety data will be entered onto study CRFs from laboratory report forms. Visit dates and laboratory procedure dates will be recorded on all forms. All participants will be assigned a unique screening number and participant identification number at study enrollment – one or both of these numbers will be included in the CRF and in the trial database and will serve to link study data to specific individuals. CRFs will be entered, verified for accuracy, linked by study participant number, and managed using database management software, with proper security and controls and the ability to identify who is entering or making changes to the data in the system.

*Source data and Participant Files*

Source documents provide evidence for the existence of the participant and substantiate the integrity of the data collected. Source documents are filed at the investigator’s site.

The investigator has to keep a written participant file for every participant participating in the clinical study. In this participant file, the available demographic and medical information of a participant is documented, including but not limited to: name, date of birth, sex, height, weight, participant history, concomitant diseases and concomitant drug(s) (including changes during the study), statement of entry into the study, study identification, randomization number, the date of informed consent, all study visit dates, predefined performed examinations and clinical findings, observed AEs, and reason for withdrawal from the study, if applicable.

It should be possible to verify the inclusion and exclusion criteria for the study from the available data in this file.

It must be possible to identify each participant by using this participant file. Additionally, any other documents with source, especially original printouts of data that were generated by technical equipment have to be filed. This includes laboratory reports. All these documents have to bear at least the participant identifier and the printing date printed by the recording device to indicate to which participant and to which study procedure the document belongs. The medical evaluation of such records should be documented as necessary, signed/initialed and dated by the investigator.

Data reported on the CRFs that are transcribed from source documents must be consistent with the source documents or the discrepancies must be explained.

